### Secondary aims

We will conduct exploratory studies to investigate:

1. The role of BV at baseline on the development of PID over 12 months.

2. In women with untreated chlamydial infection, the proportion who have persistent infection or develop PID within 12 months.

3. The annual incidence of chlamydia infection in women without chlamydia at baseline who return follow up postal samples.

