### Follow up after one year

A year after recruitment, participants were asked to complete a secure online questionnaire about PID symptoms during the previous 12 months. Those not responding or not providing an email address were sent the questionnaire by post backed up by telephone reminders. In order to maximise follow up, consent forms requested details of home and term time addresses and telephone numbers, email, mobile phone number, college course and GP address. The questionnaire asked about possible symptoms of, or treatment for, PID or other STI, any additional STI testing, and hospital and GP attendances in the past year. Women who reported no symptoms of possible PID on their questionnaire had no further follow up. For women who did not return a questionnaire and those who reported consulting a health professional for possible symptoms of PID we sent a questionnaire to their GPs. This asked GPs to search both their records and any hospital letters during the 12 month period after recruitment for possible symptoms of PID. In addition, all women who agreed on their follow up questionnaire to return a further swab were sent one in the post. These postal samples were analysed immediately and infected women referred for treatment.

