### Analysis Plan

For the primary analysis, we will estimate the relative risk of developing PID in the 12 months after recruitment in the intervention group compared with the control.

In secondary analyses, we will conduct an exploratory logistic regression to adjust the RR of development of PID for the presence of baseline BV.

We will conduct further exploratory analyses to assess:

In women with untreated chlamydial infection, the proportion (95%CI) who have persistent infection or develop PID within 12 months.

The annual incidence (95%CI) of chlamydia infection in women without chlamydia at baseline who return follow up postal samples.

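### The exploratory annual incidence of chlamydia appears to rest on one postal swab, which gives new positivity at follow-up rather than incidence

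*Protocol article*

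**What the plan says.** The quantity appears three times in the Protocol article: under Secondary aims ("The annual incidence of chlamydia infection in women without chlamydia at baseline who return follow up postal samples"), in almost the same words under Secondary outcome measures, and in the Analysis Plan ("The annual incidence (95%CI) of chlamydia infection in women without chlamydia at baseline who return follow up postal samples").

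The measurement is described under Follow up after one year. The timing is set by the questionnaire: "A year after recruitment, participants were asked to complete a secure online questionnaire about PID symptoms during the previous 12 months". After that, "all women who agreed on their follow up questionnaire to return a further swab were sent one in the post", and "These postal samples were analysed immediately and infected women referred for treatment". No test between the baseline swab and this one is described.

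Two other statements bear on the point. The follow-up questionnaire also sought information on infections found outside the trial: "The questionnaire asked about possible symptoms of, or treatment for, PID or other STI, any additional STI testing". And the Analysis Plan treats persistence as something to be estimated: "In women with untreated chlamydial infection, the proportion (95%CI) who have persistent infection or develop PID within 12 months".

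**The concern.** A woman who was negative at baseline, caught chlamydia in month 4 and was treated in month 6 would be negative on the postal swab. So would a woman who cleared the infection unaided. A swab-only count records both as never infected, yet both are incident cases.

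The article gives reason to expect such women. The persistence aim assumes that some infections do not last the year. The information leaflet quoted under Ethical issues urges women who may be at risk to have a check-up during the trial. The Discussion also suggests that outside testing was common: early in recruitment 136 women were excluded for a chlamydia test in the previous 3 months, against 1367 who were eligible. If those 136 were otherwise eligible (an assumption), 136 / (136 + 1367) = 136 / 1503 = 9% had been tested in one 3-month window. That counts tests, not infections, but it shows that detection between the two swabs is realistic.

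The word annual is also not secured. The swab goes out only after the 12-month questionnaire has come back, and non-responders were chased by post and telephone, so the interval may be longer than a year.

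At stake is the meaning of one natural-history estimate. Readers would compare a figure labelled annual incidence with true incidence rates, although it may measure something else.

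**Working it through.** The article states no chlamydia incidence, clearance or treatment rate, so there is no figure of its own to reproduce. The calculation below is an illustration on assumed rates.

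**Inputs**
- From the article: baseline-negative women; one later swab; swab sent after the 12-month questionnaire.
- Assumed: infection at a constant rate L per year, and removal (clearance or treatment) at a constant rate m per year.

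**Formulas**
- True 12-month cumulative incidence of first infection: C = 1 − exp(−L).
- Proportion positive on one swab at t years: P(t) = L / (L + m) × [1 − exp(−(L + m) t)].
- Share captured: P(t) / C.

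**Swab at exactly 12 months, L = 0.05**

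C = 1 − exp(−0.05) = 4.88%. Worked example for m = 0.5: P(1) = 0.05 / 0.55 × [1 − exp(−0.55)] = 3.85%, and 3.85 / 4.88 = 0.79.

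| m per year | infections removed within a year of onset, 1 − exp(−m) | P(1) | P(1) / C |
|---|---|---|---|
| 0 | 0% | 4.88% | 1.00 |
| 0.25 | 22% | 4.32% | 0.89 |
| 0.5 | 39% | 3.85% | 0.79 |
| 0.69 | 50% | 3.53% | 0.72 |
| 1.0 | 63% | 3.10% | 0.63 |
| 2.0 | 86% | 2.13% | 0.44 |

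With L = 0.03 or L = 0.10 the ratios change by no more than about 0.01. The shortfall therefore depends on the removal rate and hardly at all on the infection rate.

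**Later swab, not adjusted for time, L = 0.05 (ratio to the 12-month C)**

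| m per year | 12 months | 15 months | 18 months | 24 months |
|---|---|---|---|---|
| 0.25 | 0.89 | 1.07 | 1.24 | 1.54 |
| 0.5 | 0.79 | 0.93 | 1.05 | 1.24 |
| 0.69 | 0.72 | 0.84 | 0.93 | 1.07 |
| 1.0 | 0.63 | 0.71 | 0.77 | 0.86 |

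A delay can cancel or reverse the shortfall, but by adding time at risk, not by recovering missed infections. At 18 months with m = 0.5, P = 5.11%, while cumulative incidence over the same 18 months is 1 − exp(−0.05 × 1.5) = 7.23%. The swab then captures 5.11 / 7.23 = 0.71 of the infections in its own interval, less than the 0.79 at 12 months. Handling the interval length and handling the removed infections are two separate corrections.

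**The case against.** The strongest reply is that the article never states the numerator. It names a quantity and a population. It does not say that a case needs a positive postal swab, or how time at risk is counted. Swabs went only to women who agreed on the questionnaire, so questions on STI treatment and on "any additional STI testing, and hospital and GP attendances in the past year" were put to the very women in the denominator, and nothing bars use of their answers. Such details may sit in a fuller protocol or SAP that is not shown. This stands to the extent that the swab-only count is an inference, drawn from the restriction to swab returners and from the absence of any other follow-up test. It does not remove the point: the article attaches the label annual incidence to a described measurement that, taken alone, does not yield it.

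A reader might go further and infer any of the following. The document does not support them.

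- *That the estimate is certainly too low, by a known amount.* With a swab at exactly 12 months and assumed mean durations of 24 to 6 months, (D/12)(1 − exp(−12/D)) gives 79% to 43% of infections still present, a shortfall of 21% to 57%. That range follows wholly from the chosen durations and the exact timing. A later swab can reverse the sign, and selective return of swabs could act in either direction.
- *That the plan discards the questionnaire information.* It is silent on its use.
- *That GP records could supply the missing cases.* GPs were contacted only for questionnaire non-responders and for women who had consulted for possible PID symptoms, and were asked about PID symptoms. A swab returner with a symptomless interval infection would have no GP data.
- *That restricting the analysis to swab returners is an error.* The restriction is stated openly each time.
- *That the figure will set rescreening intervals.* The Conclusion claims only a contribution to the evidence base for national sexual health strategy.

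**Conclusion.** The point holds as a mismatch between label and measurement. As described, the analysis appears to yield the proportion newly positive at one follow-up time among baseline-negative women who returned a swab. For any removal rate above zero, that proportion is below the cumulative incidence over the same interval. With a swab at exactly 12 months the share captured runs from about 89% down to 44% for removal rates of 0.25 to 2.0 per year, and is about 72% if half of infections are gone within a year of onset. These figures rest on assumed constant rates and concern clearance and treatment only.

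The net direction of error in the reported figure cannot be settled from the article, because the interval may exceed a year and swab return may be selective. The analysis is exploratory, and the primary comparison of PID between the groups does not depend on it.

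**What to change.** 1. Report the swab result as the proportion newly positive at follow-up among baseline-negative responders, with its 95% CI and the distribution of the actual baseline-to-swab interval.
2. If an incidence rate is also given, base it on person-time from each woman's actual interval, and say that this corrects for interval length but not for infections that cleared or were treated.
3. Add a sensitivity analysis that also counts chlamydia infections diagnosed or treated in the interval, as reported on the 12-month questionnaire.

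The cost is a change of wording and a small extra analysis; no new contact with participants is needed. The drawback lies in step 3: the reports are the women's own and may not name the organism or give a date. The result should therefore stand beside the swab figure and not replace it. GP data should not be relied on for this count, for the reason given above.

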### Ethical issues

The POPI trial was approved by Wandsworth Research Ethics Committee in 2003 (Ref 03.0054). The main ethical issue was that samples from control women were stored and not tested for chlamydia for 12 months. This was clearly explained to the women before they participated and repeated on the information sheet and consent form (attached). In addition an extra copy of the information sheet was posted to their home address. The patient information leaflet (please see additional file 1) stated:

"What are the risks of taking part? When you sign the consent form you should note that your vaginal sample will be tested for a sexually transmitted infection called chlamydia. However the test may not be done for a whole year. You could have chlamydial infection without experiencing any symptoms. This could lead to pelvic inflammatory disease with a risk that you have chronic pelvic pain, become infertile, or that if you become pregnant that you have an ectopic pregnancy (a pregnancy in a fallopian tube which can be fatal). *This is why if you could have been at risk of infection, or have any symptoms which could be due to a sexually transmitted infection, it is vital that you have a check up at a genitourinary clinic even if you are participating in the study"*.

## Discussion

Recruiting young women to a trial of chlamydia screening proved much harder than anticipated. We developed new techniques to market the trial to students, particularly recruiting from lectures and offering lollipops[13,14]. To achieve our sample size we also had to extend recruitment to 20 educational institutions and to prolong the recruitment period to 2 years (from September 2004 to October 2006.) For the first 4 months of recruitment, peer recruiters completed response rate forms. Of 2323 women approached 41% (956) were ineligible: 41% (n = 390) had never had sexual intercourse, 24% were aged <16 (n = 19) or >27 years (n = 206), and 14% (n = 136) had been tested for chlamydia in the previous 3 months. The response rate in those eligible was 32% (440/1367). Reasons for refusal (n = 927) included "not interested" 35%, "too busy" 31%, "don't want to provide swab" 13%. Recruitment rates seemed to improve later in the trial and were over 60% in the last three sessions[14].

## Conclusion

The trial will be the first to show if screening for chlamydial infection can reduce the incidence of PID in a British population. It will also show if non-invasive screening of high risk, difficult to access groups such as women aged <20 and those from black ethnic minorities is feasible outside health care settings. Over 40% of young people in the UK now attend higher education adding to the generalisability of the results. If the intervention is effective, extending such screening programmes to the community should help to reduce the burden of PID. Finally by providing new information on both the effectiveness of screening and on the natural history of chlamydial infection and the influence of BV, the study will contribute to the evidence base for the UK National Strategy for Sexual Health. The trial will report in December 2008.

## Abbreviations

PID: pelvic inflammatory disease; POPI trial: Prevention of Pelvic Infection trial; BV: bacterial vaginosis; TMA: transcription mediated amplification; RR: relative risk; GP: general practitioner; STI: sexually transmitted infection; GUM: Genitourinary Medicine.
